## Abstract

This protocol describes a laboratory-based experimental method for investigating whether exposure to contagious yawning stimuli is associated with measurable changes in subjective and physiological markers of sleepiness. The protocol employs a randomized within-subject crossover design comparing human versus digital character yawning stimuli, each presented with and without auditory cues. The method integrates validated subjective sleepiness assessments with multimodal physiological sensing including cardiovascular, electrodermal, pupillary, thermal, and neural activity measures. This protocol addresses a methodological gap in yawning research by shifting focus from yawning occurrence to downstream sleepiness-related state changes associated with yawning stimuli exposure, while also examining whether digitally presented yawning is comparable to human yawning.

Standardized experimental protocol for assessing sleepiness associated with contagious yawning stimuli exposure

Integration of subjective measures with multimodal physiological sensing for comprehensive state assessment

Direct comparison of yawning stimuli of human versus digital characters

## Specifications table

**Table utbl0001:** 

**Subject area**	Psychology
**More specific subject area**	Psychophysiology, contagious behavior, sleep health, human-computer interaction
**Name of your protocol**	Catch-a-yawn
**Reagents/tools**	▪ Smart wristband (EmbracePlus, Empatica Inc., US) ▪ Eye-tracking system (PupilCore, PupilLabs GmbH, Germany) ▪ Functional near-infrared spectroscopy system (Brite, Artinis Medical Systems, The Netherlands) ▪ Smartwatch (Google Pixel Watch, Google LLC, US) ▪ Video recording equipment ▪ Karolinska Sleepiness Scale (KSS) ▪ Munich Chronotype Questionnaire (MCTQ) ▪ Pittsburgh Sleep Quality Index (PSQI) ▪ Big Five Personality Test (BFPT)
**Experimental design**	Laboratory-based randomized within-subject crossover design with four experimental conditions: video of human yawning with sound, video of human yawning without sound, video of digital character yawning with sound, video of digital character yawning without sound. Each participant completes two sessions on separate days with randomized condition order.
**Trial registration**	Not applicable.
**Ethics**	This protocol was approved by the Ethics Review Board at Kyoto University of Advanced Science. Informed consent will be obtained from all participants prior to participation. All data will be anonymized and stored securely. Video recordings will be used only for behavioral coding and will be destroyed immediately after feature extraction.
**Value of the Protocol**	▪ Provides a systematic, replicable method for investigating sleepiness under contagious yawning stimuli using multimodal physiological assessment ▪ Addresses methodological gaps in yawning research by integrating subjective and objective sleepiness measures within a controlled experimental framework ▪ Establishes standardized procedures for comparing human versus digital character behavioral stimulus, which can inform the design of AI-driven sleep health technologies

## Background

Yawning is a ubiquitous human behavior that has been studied across both animal and human research contexts [1,2]. Beyond occurring spontaneously, yawning is socially contagious. Observing or hearing others yawn reliably increases the likelihood of yawning in the observer [[3], [4], [5]]. Contagious yawning has been linked to social cognition, empathy, and physiological regulation [3], and its neural mechanisms have been examined in both animals and humans [4,5]. Functional MRI research has implicated regions associated with social cognition and self-referential processing, including the medial prefrontal cortex, posterior cingulate cortex, and precuneus [[4], [5], [6]], as well as areas involved in attention and motor resonance. These findings suggest that contagious yawning engages networks related to both social processing and state regulation. This neurophysiological perspective motivates the inclusion of functional near-infrared spectroscopy (fNIRS) in the present study to assess prefrontal cortical activity during exposure to yawning stimuli.

Beyond its neural basis, a substantial body of research has also advanced our understanding of the physiological functions of yawning. In particular, the thermoregulatory or “brain cooling” hypothesis proposes that yawning serves to regulate brain temperature and maintain optimal neural functioning, with converging evidence from both animal and human studies [[7], [8], [9], [10]]. This perspective highlights the close relationship between yawning, arousal regulation, and physiological state changes.

Consistent with this view, experimental studies have examined how exposure to yawning stimuli influences behavior and cognition. For example, recent studies have demonstrated that viewing yawning stimuli can enhance vigilance and threat detection performance, such as improved detection of biologically relevant stimuli including snakes and spiders [[11], [12], [13]]. At the same time, yawning is commonly associated with fatigue, drowsiness, and transitions toward sleep [2,[14], [15], [16]], and prior studies have explored subjective sleepiness in relation to yawning behavior [2,14,15]. These findings suggest that yawning is closely linked to fluctuations in arousal, though its precise role in modulating internal states remains complex.

Yawning contagion is also multimodal. Although visual stimuli have been the most commonly studied, auditory contagious yawning has likewise been reported, with yawning sounds alone capable of eliciting yawning responses in listeners [17,18]. In addition, previous work has suggested that olfactory cues may contribute to yawning contagion, which further underscores the multimodal nature of this phenomenon [19]. These findings indicate that yawning can function as a socially transmitted cue across multiple sensory channels. In the present protocol, we focus specifically on visual and auditory yawning stimuli, while olfactory stimuli are not examined and are left for future investigation.

Despite these advances, comparatively fewer studies have systematically examined how exposure to yawning stimuli relates to integrated, multimodal changes in sleepiness and physiological arousal. Existing research has often focused on either behavioral outcomes (e.g., yawning occurrence or vigilance performance) or isolated measures of sleepiness, which limit the ability to characterize how yawning stimuli are associated with internal states across subjective and physiological domains simultaneously. A multimodal approach combining behavioral, subjective, and physiological measures may therefore provide a more comprehensive understanding of state changes related to exposure to contagious yawning stimuli.

At the same time, contemporary human–computer interaction increasingly involves digital agents, avatars, and animated representations of human behavior. Advances in AI and computer graphics have enabled these systems to display human-like expressions and social cues, and they are now widely deployed in digital health, education, customer support, and other interactive environments [20,21]. Such systems often rely on subtle behavioral signals to influence user engagement, affect, and cognitive state. Within this context, yawning represents a particularly intriguing but underexplored behavioral cue.

Previous studies have demonstrated that digitally presented yawning videos can elicit contagious yawning responses in humans [22,23], and even across species, such as in chimpanzees and orangutans exposed to digital or android yawning stimuli [24,25]. However, it remains unclear whether digitally presented yawning stimuli, particularly those generated by animal characters, are associated with sleepiness-related responses when assessed using multimodal psychophysiological measures.

Understanding whether exposure to yawning stimuli is associated with changes in sleepiness has important implications for both sleep research and the design of technologies intended to modulate arousal or relaxation [2]. Accordingly, this study seeks to advance this line of research by examining yawning videos featuring either humans or digital characters, presented with and without auditory cues, and assessing their associations with subjective and physiological indicators of sleepiness under controlled conditions. The protocol was developed to investigate four research questions: (1) whether exposure to human yawning videos is associated with sleepiness-related responses, (2) whether digital character yawning elicits comparable effects, (3) whether auditory yawning cues modulate these responses, and (4) how individual differences influence these associations.

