Exploratory outcomes will include behavioral indicators of sleepiness, such as yawning occurrence and instances of sleep onset observed during the experiment. Additional exploratory analyses will examine the relationship between yawning behavior and both subjective and physiological outcomes. These relationships will be modeled using mixed-effect approaches where appropriate, which allows for the inclusion of both within-subjects (e.g., condition, time) and between-subjects (e.g., chronotype, baseline sleep quality) factors.

Statistical significance will be evaluated using two-sided tests with an alpha level of 0.05 unless otherwise specified. Results will be reported using effect sizes (e.g., estimated mean differences as quantified by Cohen’s *d* or Hedge’s *g*) alongside 95% confidence intervals and p-values. Given the exploratory nature of several outcomes, findings will be interpreted with appropriate caution, and emphasis will be placed on the direction, magnitude, and consistency of observed effects rather than statistical significance alone. The data analysis plan is summarized in Table 2.

**Table 2 tbl0002:** Data analysis plan.

Analysis Level	Procedure
Primary outcome analysis	▪ Analyze changes in KSS using linear mixed-effects models to account for the within-subject repeated-measures design ▪ Fixed effects will include stimulus type (human vs digital character yawning), auditory condition (with sound vs without sound), and their interaction. ▪ Subject will be included as a random effect with a random intercept to account for interindividual differences in baseline sleepiness. ▪ Where model convergence permits, random slopes for condition effects may be explored. ▪ Conduct planned comparison [50] to examine differences in subjective sleepiness between human and digital yawning stimuli, differences between auditory conditions (with vs without sound), and the interaction between stimulus type and auditory condition.
Secondary outcome analysis	▪ Apply the mixed-effects modeling framework used for primary outcome analysis to each physiological outcome, including HRV, EDA, skin temperature, pupil dynamics, and fNIRS measures. ▪ Analyses will focus on changes relative to baseline and associations with experimental conditions. ▪ Where appropriate, multiple comparison adjustments (e.g., Bonferroni or false discovery rate correction) will be reported as supplementary information.

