### Limitations

Several limitations should be acknowledged. First, the laboratory-based setting may limit ecological validity relative to real-world contexts in which yawning and sleepiness naturally occur. Second, the protocol does not include a non-yawning control condition. Although baseline and post-condition measurements allow for within-subject assessment of state changes, the absence of a neutral comparison condition limits the ability to attribute observed changes uniquely to yawning stimuli, as alternative explanations such as time-on-task effects, fatigue, or repeated exposure cannot be fully excluded. Third, while behavioral indicators of sleep onset and physiological correlates of reduced arousal will be assessed, the study does not include polysomnography. Therefore, precise sleep onset latency cannot be determined. Despite these limitations, this protocol establishes a methodological framework for investigating how human-like behavior presented by digital agents is associated with subjective and physiological states, which provides a foundation for future confirmatory studies and real-world deployments.

Findings from executing this protocol will have several important implications. From a theoretical perspective, it contributes to a more functional understanding of whether exposure to contagious yawning stimuli is associated with changes in sleepiness and arousal regulation, rather than focusing solely on yawning frequency. By integrating subjective, physiological, and behavioral indicators, the study informs ongoing debates regarding the potential role of yawning stimuli exposure in sleep-related state modulation. From an applied perspective, the findings may inform the design of non-pharmacological approaches for modulating arousal and relaxation. In particular, evidence that digitally presented yawning stimuli are associated with sleepiness-related responses would have implications for the design of AI-driven avatars, digital companions, and interactive health technologies, where subtle behavioral cues may be leveraged to influence user state without explicit instruction.

Importantly, even in the absence of strong effects, the study will help delineate the conditions under which exposure to contagious yawning stimuli is not meaningfully associated with sleepiness-related states. Such null or weak findings would provide valuable insight for refining theoretical models and informing the design of future digital interventions.

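### Research question 2 asks whether digital yawning is comparable to human yawning, but the planned contrast tests for a difference and sets no bound for judging comparability

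*Protocol article*

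**What the plan says.** Comparability is a stated aim in two places of the protocol article. Background lists as research question 2 "whether digital character yawning elicits comparable effects", and the Abstract describes the protocol as "while also examining whether digitally presented yawning is comparable to human yawning".

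The Data analysis section makes change in KSS the primary outcome. Table 2 specifies a linear mixed model: "Fixed effects will include stimulus type (human vs digital character yawning), auditory condition (with sound vs without sound), and their interaction". For the contrast at issue it says: "Conduct planned comparison [50] to examine differences in subjective sleepiness between human and digital yawning stimuli". The general rule is "Statistical significance will be evaluated using two-sided tests with an alpha level of 0.05 unless otherwise specified", and nothing different is specified for this contrast. Effect sizes are to be reported "alongside 95% confidence intervals and p-values", with the weight placed on direction, size and consistency more than on significance alone.

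The article gives no equivalence margin, smallest difference of interest, rule for reading the interval or other criterion for comparability. Separately, Limitations says that even without strong effects "the study will help delineate the conditions under which exposure to contagious yawning stimuli is not meaningfully associated with sleepiness-related states".

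**The concern.** A test of no difference can support the statement that two stimuli differ. It cannot support the statement that they are alike, because failing to reject zero shows only that the data did not exclude zero. A confidence interval can support similarity, but only against a bound chosen in advance. Without one, whoever reads the interval chooses the bound after seeing it.

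Question 2 therefore has an analysis attached that addresses a different hypothesis. If p-values alone were read, a smaller or noisier study would more often seem to show comparability. Limitations expects the results on digital yawning to inform avatars and interactive health technologies, so an unsupported statement of comparability could be carried into that work.

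**Working it through.** The article gives no sample size, SD, effect size, power or margin, so there is no figure of its own to reproduce. The check has two parts.

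**Question against analysis**

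- Question asked: are the effects comparable (Background, Abstract)?
- Hypothesis tested: is the human-digital difference zero (Table 2; two-sided, 0.05)?
- Estimate reported: effect size with 95% interval.
- Bound for reading that interval as comparable: none.

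**How often a real difference would be non-significant**

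Assumptions, none of them from the article: each participant contributes one human-minus-digital KSS difference; true mean difference d = 0.5 points; SD of that difference s = 1.2, 1.5 or 2.0; n = 20, 30 or 40. The paired t-test stands in for the mixed-model contrast.

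- SE = s/√n, and noncentrality = d/SE.
- P(non-significant) = P(|T| < t with n−1 df at 0.975), where T is noncentral t.
- Example, n = 30 and s = 1.5: SE = 1.5/√30 = 0.274; noncentrality = 0.5/0.274 = 1.83; critical t = 2.045; P = 58%. The 95% half-width is 2.045 × 0.274 = 0.56.

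| n | s = 1.2 | s = 1.5 | s = 2.0 |
|---|---|---|---|
| 20 | 58% | 71% | 81% |
| 30 | 40% | 58% | 74% |
| 40 | 27% | 46% | 66% |

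**What a comparability rule would deliver**

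Two one-sided tests at 0.05 each are equivalent to requiring the 90% interval to lie within ±m. Power is computed at a true difference of zero, as the probability that |estimate| + t(0.95) × estimated SE is below m. For n = 30, s = 1.5, m = 1 the expected 90% half-width is 1.699 × 0.274 = 0.465, so the estimate must fall within about ±0.535; the power is about 95%.

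| n | m = 1.0: s = 1.2 / 1.5 / 2.0 | m = 0.5: s = 1.2 / 1.5 / 2.0 |
|---|---|---|
| 20 | 95% / 78% / 39% | 16% / 3% / under 1% |
| 30 | over 99% / 95% / 70% | 44% / 14% / under 1% |
| 40 | over 99% / 99% / 86% | 65% / 33% / 3% |

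The margins 1.0 and 0.5 are illustrations, not proposals. By normal approximation, 80% power at m = 0.5 needs n = (s × (1.645 + 1.282)/0.5)², which is 78 at s = 1.5 and 138 at s = 2.0. At m = 1.0 it needs 20 and 35.

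**The case against.** The strongest defence is that the protocol never commits to the error. A reader might infer that a non-significant p-value will be reported as comparability, but no sentence says so; the quoted words are a research question. Nor is a p-value the only output: effect sizes and 95% intervals are planned and significance alone is played down, so a wide interval would be visible. Overview and Data analysis also describe the aim as relative differences between conditions, which is estimation. All of this stands, and it lowers the severity. It does not supply a criterion: an interval without a bound fixed beforehand still leaves comparability undecided.

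A reader might also take the Limitations sentence on null findings as a plan to misread the human-digital contrast. It is not about that contrast. It concerns exposure and sleepiness in general and speaks of weak or absent effects, not of non-significance.

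It may further be said that a margin could sit in a fuller protocol or analysis plan that is not shown. The point does not rest on that silence. The article itself fixes model terms, contrast, sidedness and alpha, and the contrast so fixed tests for a difference while the stated question is comparability.

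Finally, an equivalence rule is not free. The second table shows that it could be badly underpowered, and a 1-point margin would often admit a true half-point difference as comparable. That is a fair limit on the remedy and is the reason to offer a second one.

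**Conclusion.** The point holds in a limited form. The stated question is comparability, the planned inference is a test for differences, and no bound connects the two. As written, the plan can show that human and digital yawning differ and can estimate by how much. It gives no valid basis for concluding that they are comparable.

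The size depends wholly on assumed inputs: with a true difference of 0.5 KSS points, SD 1.2 to 2.0 and n 20 to 40, non-significance has probability 27% to 81%. The logical gap does not depend on those values.

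This is a should-fix. The difference contrast and its interval are legitimate analyses. What needs changing is the match between the question and the criterion.

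**What to change.** Choose one of two routes before data collection.

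1. **Keep the comparability question.** State a KSS margin for the human-digital contrast and justify it as the smallest difference that matters. Conclude comparability only if the 90% interval from the mixed model lies wholly within the margin (two one-sided tests at 0.05 each). Keep the difference test beside it, and report a result that meets neither criterion as inconclusive.
2. **Drop the comparability claim.** Reword question 2 and the Abstract as estimating the human-digital difference with its 95% interval.

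Separately, tie the Limitations sentence on null findings to the width of the reported intervals. The human-digital margin should not be used for it. Since Overview excludes a non-yawning control, similarity of the two stimuli would also not show that either one affects sleepiness, and the report should say so.

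Cost: route 2 needs only rewording. Route 1 needs a margin with its justification and one more reading of an interval the model already yields. Its downside is that an inconclusive result may be likely: over n 20 to 40 and SD 1.2 to 2.0, power at zero true difference runs from 39% to over 99% for a 1-point margin and from under 1% to 65% for a 0.5-point margin. Whether the planned sample suffices cannot be judged from the article, so the margin should be checked against the intended n before route 1 is chosen.

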## Description of protocol

### Overview

This protocol employs a laboratory-based, randomized within-subject crossover experimental design to examine the associations between contagious yawning stimuli exposure and subjective and physiological indicators of sleepiness. The protocol follows a 2 × 2 factorial structure manipulating: (1) stimulus type (human vs. digital character yawning) and (2) auditory content (with vs. without sound), yielding four experimental conditions.

Participants complete two sessions on separate days. In one session, they view human yawning videos under both auditory conditions in randomized order. In the other session, they view yawning videos of digital characters under the same auditory conditions. The order of sessions (human first vs. digital first) will be counterbalanced across participants. The order of conditions will be randomized and counterbalanced to minimize systematic order effects.

A within-subject design was selected to maximize sensitivity to condition-related differences while controlling for interindividual variability in baseline sleepiness, circadian preference, and autonomic functioning. To mitigate potential fatigue or habituation effects, experimental sessions will be conducted on separate days with a minimum interval of one-day between sessions.

The protocol is designed to examine relative differences across yawning stimulus conditions and within-subject changes over time, rather than to isolate yawning-specific causal effects relative to neutral stimulus exposure. Accordingly, non-yawning control conditions are not included. This design enables focused comparison across stimulus modalities and representations while maintaining a manageable experimental duration within a multimodal physiological recording context, which is consistent with prior studies using contagious yawning stimuli [26,27]. Pre-stimulus baseline recordings will be obtained prior to each condition, which allows within-subject quantification of changes relative to a stable resting reference.

As illustrated in Fig. 1, the protocol consists of three sequential phases: (1) pre-experiment assessment, (2) two experimental sessions conducted on separate days, and (3) post-experiment assessment and debriefing. Each stimulus condition has a duration of approximately 5 min, resulting in a total stimulus exposure of approximately 10 min per session. This duration is selected to assess physiological state changes associated with yawning stimulus exposure while limiting fatigue and time-on-task effects, and is consistent with the 3–5 min range commonly employed in contagious yawning research [15,22].

